## Abstract

**Background:**

Recent studies have revealed that many discharged patients with COVID-19 experience ongoing symptoms months later. Rehabilitation interventions can help address the consequences of COVID-19, including medical, physical, cognitive, and psychological problems. To our knowledge, no studies have investigated the effects of rehabilitation following discharge from hospital for patients with COVID-19.

**Objective:**

The specific aims of this project are to investigate the effects of a 12-week exercise program on pulmonary fibrosis in patients recovering from COVID-19. A further aim will be to examine how Chinese herbal medicines as well as the gut microbiome and its metabolites regulate immune function and possibly autoimmune deficiency in the rehabilitation process.

**Methods:**

In this triple-blinded, randomized, parallel-group, controlled clinical trial, we will recruit adult patients with COVID-19 who have been discharged from hospital in Hong Kong and are experiencing impaired lung function and pulmonary function. A total of 172 eligible patients will be randomized into four equal groups: (1) cardiorespiratory exercise plus Chinese herbal medicines group, (2) cardiorespiratory exercise only group, (3) Chinese herbal medicines only group, and (4) waiting list group (in which participants will receive Chinese herbal medicines after 24 weeks). These treatments will be administered for 12 weeks, with a 12-week follow-up period. Primary outcomes include dyspnea, fatigue, lung function, pulmonary function, blood oxygen levels, immune function, blood coagulation, and related blood biochemistry. Measurements will be recorded prior to initiating the above treatments and repeated at the 13th and 25th weeks of the study. The primary analysis is aimed at comparing the outcomes between groups throughout the study period with an α level of .05 (two-tailed).

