Evaluate the effects of cardiorespiratory exercise and Chinese herbal medicine, both individually and in a combination, on rehabilitation on pulmonary function among patients with COVID-19 through four intervention groups, including a cardiorespiratory exercise plus Chinese herbal medicines group, a cardiorespiratory exercise group in isolation, a Chinese herbal medicines group, and a waiting list control group (primary outcome). We hypothesize that the combination of cardiorespiratory exercise and Chinese herbal medicines will more greatly facilitate the rehabilitation of patients with COVID-19.Reveal whether and how the gut microbiome plays a role in the effects of cardiorespiratory exercise and Chinese herbal medicines, both individually and in combination, on the rehabilitation of impaired pulmonary function. We hypothesize that the combination of cardiorespiratory exercise and Chinese herbal medicines will better modulate the gut microbiome and the related metabolites and thus better mediate the effects.Assess the effects of cardiorespiratory exercise and Chinese herbal medicines on immune functions, both individually and in combination, on the rehabilitation of other relevant symptoms and signs of COVID-19. We hypothesize that the combination of cardiorespiratory exercise and Chinese herbal medicines will better modulate the immune function and thus better mediate the effects.Evaluate the effects of cardiorespiratory exercise and Chinese herbal medicines, both individually and in combination, on recovery from mental health-related outcomes (loneliness, stress, anxiety, depression) and on quality of life (QoL). We hypothesize that the combination of cardiorespiratory exercise and Chinese herbal medicines will better help postdischarge patients in recovery from mental health-related outcomes and improve their QoL.Assess the lasting effects of cardiorespiratory exercise and Chinese herbal medicines after a 12-week follow-up period. We hypothesize that some effects (eg, dyspnea, mental health-related outcomes, QoL) will be sustainable, while others (outcomes sensitively responded to cardiorespiratory exercise, eg, physical fitness, lung function) will partially relapse after the intervention cessation.

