## Methods

### Study Design

The proposed study will be a triple-blinded randomized controlled trial comprising four groups: (1) a cardiorespiratory exercise plus Chinese herbal medicines group, (2) a cardiorespiratory exercise group, (3) a Chinese herbal medicines group, and (4) a waiting list group. The target population will be postdischarge adult patients recovering from COVID-19 who were diagnosed with pulmonary impairments. Recruitment will take place in Hong Kong via our International Rehabilitation Network Center for Patients With COVID-19. The proposed rehabilitation period will last for 12 weeks, with a 12-week follow-up [14]. Primary outcomes will include the clinical symptoms of pulmonary fibrosis (dyspnea, fatigue, lung function, blood oxygen levels, immune function, blood coagulation, and related blood biochemistry). Blood biochemistry will be further analyzed using unique metabolomics techniques to identify potential synergies related to immune function response to the interventions [15]. We will investigate glucose metabolism and its association with the degree of infection and prognosis. We will also profile the gut microbial metabolome to establish associations between (virus-induced) dysbiosis and the outcomes of COVID-19 infection. Pulmonary function tests will be completed using clinical spirometry, as outlined by the American Thoracic Society. Blood gas levels, immune function, and coagulation levels of the patients will be measured pre- and post-intervention in venous blood samples [16]. The trial has been registered on ClinicalTrials.gov (NCT04572360). A flow diagram of the trial is shown in Figure 1.

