### Statistical Analysis

A generalized linear mixed model will be used to compare between-group differences in changes of outcome variables at the 12- and 24-week periods of the study, where group and time are the two factors of interest. Mediating effects of the gut microbiome and immune function tests will be determined by fitting linear regression models for pulmonary and other outcomes, respectively. A significance level of 0.05 will be adopted (two-tailed test). Intention-to-treat procedures will be applied to the data sets obtained. Missing data will be imputed using multiple imputations with chained equations, except for those from dropouts, which will be imputed with the baseline data. Data will be scrutinized for normal distribution prior to data analysis. Sensitive analyses, such as per-protocol analysis, as-treated analysis, and analysis for complete cases, will only be performed to assess the robustness of the data analyses.

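### Seven or eight domains are called primary, the definition changes between sections, and one undivided two-sided 0.05 covers them all, although 172 patients is the size for a single test

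*Protocol article*

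**What the plan says.** All references are to the protocol article.

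- **Abstract, Methods:** "Primary outcomes include dyspnea, fatigue, lung function, pulmonary function, blood oxygen levels, immune function, blood coagulation, and related blood biochemistry". The same paragraph sets the error rate: "The primary analysis is aimed at comparing the outcomes between groups throughout the study period with an α level of .05 (two-tailed".
- **Study Design:** the primary outcomes are given as "dyspnea, fatigue, lung function, blood oxygen levels, immune function, blood coagulation, and related blood biochemistry". Pulmonary function, which the Abstract lists beside lung function, is not in this list.
- **Introduction, objectives:** the primary label appears once, at the end of the comparison of arms in the pulmonary-function objective: "and a waiting list control group (primary outcome". Immune function has a separate, later objective without that label: "Assess the effects of cardiorespiratory exercise and Chinese herbal medicines on immune functions, both individually and in combination".
- **Statistical Analysis:** a generalized linear mixed model with group and time as factors, covering changes at 12 and 24 weeks, and then "A significance level of 0.05 will be adopted (two-tailed test".
- **Sample Size Calculation:** effect size 0.8 from a meta-analysis of exercise interventions on dyspnea and exercise capacity, significance level 0.05, power 90%, drop-out 20%, giving 172 patients (43 per group). A re-estimation from pilot data is planned.
- **Table 2:** several domains hold more than one measure. Lung function alone has five (FVC, FEV1, FEV1/FVC, FeNO, DLCO).

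**The concern.** The article gives more than one answer to what the trial is meant to show. Under the objectives, success is an effect on pulmonary function. Under the Abstract and Study Design, it could equally be an effect on immune function, coagulation or blood biochemistry. The stated 0.05 is not divided among these domains, and no contrast or visit has priority. A favourable result in any one domain could therefore be reported as a positive primary outcome, and the pulmonary question in the first objective would have no protected test. The sample size also cannot be matched to a defined primary analysis, and the planned re-estimation would inherit that gap.

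**Working it through.** **1. Reproduce the sample size.** Inputs from Sample Size Calculation: d = 0.8, two-sided alpha 0.05, power 90%, drop-out 20%.

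- Normal approximation: 2 × (1.960 + 1.282)² / 0.8² = 32.8, so 33 per group.
- Two-sample t-test: 33.8, so 34 evaluable per group.
- Drop-out: 34 / (1 − 0.20) = 42.5, so 43 per group.
- Four groups: 4 × 43 = 172, exactly the stated figure.

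So 172 is the size for one outcome, one pairwise contrast and one visit at the full 0.05.

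**2. Set the definitions side by side.**

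| Place | What is primary |
|---|---|
| Abstract | 8 domains |
| Study Design | 7 domains |
| Introduction, objectives | pulmonary function only |

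The difference between eight and seven may be one domain named twice. The difference between the objectives and the two lists is substantive.

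**3. Chance of at least one false positive with independent tests at 0.05:** 1 − 0.95^k.

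- k = 7: 30.2%. k = 8: 33.7%.
- k = 48 (8 domains × 3 contrasts against waiting list × 2 visits): 91.5%.
- k = 96 (8 domains × 6 pairs × 2 visits): 99.3%.

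**4. Allow for shared arms and correlation.** This is a simulation under no effect, with four arms, 34 per arm and 20,000 runs. The article gives no correlations. Those between outcomes (0, 0.3, 0.6) and between visits (0.7) are assumptions.

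| Scheme | 8 domains (0 / 0.3 / 0.6) | 7 domains (0 / 0.3 / 0.6) |
|---|---|---|
| One contrast, one visit, per domain | 33 / 30 / 23% | 30 / 27 / 21% |
| One joint group test over both visits, per domain | 34 / 31 / 24% | 31 / 28 / 22% |
| Three contrasts against waiting list, both visits | 83 / 80 / 66% | 80 / 75 / 64% |
| All six pairs, both visits | 95 / 93 / 82% | 93 / 90 / 80% |

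Every entry is at least four times the nominal 5%.

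**5. Power if several tests stay primary.** Two-sample t-test, d = 0.8, 34 evaluable per group, at the first Holm step (0.05/m, the same as Bonferroni). The total for 90% power is 4 × (evaluable n / 0.8, rounded up).

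| Tests m | Alpha | Power at 34 per group | Evaluable n for 90% | Total |
|---|---|---|---|---|
| 1 | 0.05 | 90% | 34 | 172 |
| 2 | 0.025 | 84% | 41 | 208 |
| 3 | 0.0167 | 80% | 44 | 220 |
| 6 | 0.0083 | 72% | 50 | 252 |
| 8 | 0.00625 | 68% | 53 | 268 |

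**The case against.** The strongest reply is that the article never says each pair of arms is tested separately at each visit. It describes a mixed model with group and time and a comparison throughout the study period, which is compatible with one joint test per outcome. That stands, so the false-positive risk has to be given as a range tied to a testing scheme.

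Three stronger readings are tempting, and the article supports none of them.

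- A reader might expand the domains through Table 2 to about 21 primary variables. That mapping is an inference. No section calls BDNF, corticosterone, insulin or the cytokines individually primary, and the Blood Biochemistry section introduces the first two and the cytokines as markers of emotional disturbance.
- A reader might object that immune function is both a primary outcome and a mediator. That is not an error, because a variable can be a trial outcome and also a candidate mechanism for another outcome.
- A reader might treat the lack of a multiplicity procedure as the fault. It could stand in an analysis plan that is not shown, so its absence alone is no finding.

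What remains is in the text itself: conflicting definitions of primary, an affirmative undivided 0.05, and a sample size for one test. An unseen analysis plan could choose among the definitions, but it would not make these sections agree.

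**Conclusion.** The point holds as an inconsistent, multiple primary definition under a single 0.05. With one test per domain, the chance of at least one false-positive primary result is about 21–34%. It rises to about 64–83% for three contrasts against waiting list at both visits, and to about 80–95% for all six pairs at both visits. These figures rest on seven or eight domains, assumed outcome correlations of 0 to 0.6 and an assumed visit correlation of 0.7.

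A reader might infer that a false-positive primary result is near certain. That needs every pairwise contrast at both visits to count as its own 0.05 test with nearly independent outcomes (99% for 96 fully independent tests), and the article does not fix that scheme. Even the most lenient scheme in the table is well above 5%, and the 90% power applies to one test only.

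**What to change.** Use one primary definition in the Abstract, the objectives, Study Design, Sample Size Calculation and Statistical Analysis, naming the variable, the contrast and the time point. One option that follows from the first objective is a single pulmonary-function measure at week 13, either FVC or DLCO as percent predicted (both are already eligibility measures), for one named contrast at two-sided 0.05. The other domains and week 25 then become secondary or exploratory.

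If more than one outcome or contrast stays primary, state the alpha allocation, for example Holm, and restate the power or the sample size from the table in the working.

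In either case, recheck the effect size. The 0.8 was taken from dyspnea and exercise capacity, so it does not carry over automatically to FVC or DLCO. The re-estimation already planned in Sample Size Calculation is the place to do this.

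With one primary test, the cost is a change of wording before unblinding, and fewer outcomes can be called primary. With several, the stated power falls or the total rises, for example to 208 for two tests or 252 for six at d = 0.8. The recheck of the effect size may also make the stated power less favourable.

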**Results:**

The trial has been approved by the university ethics committee following the Declaration of Helsinki (approval number: REC/19-20/0504) in 2020. The trial has been recruiting patients. The data collection will be completed in 24 months, from January 1, 2021, to December 31, 2022.

**Conclusions:**

Given that COVID-19 and its sequelae would persist in human populations, important findings from this study would provide valuable insights into the mechanisms and processes of COVID-19 rehabilitation.

**Trial Registration:**

ClinicalTrials.gov NCT04572360; https://clinicaltrials.gov/ct2/show/NCT04572360

**International Registered Report Identifier (IRRID):**

PRR1-10.2196/25556

## Introduction

In January 2020, the World Health Organization announced the outbreak of a novel coronavirus disease, called COVID-19. The COVID-19 pandemic has had devastating impacts globally, with 39,944,882 confirmed cases and 1,111,998 deaths recorded by October 20, 2020. Indeed, the number of cases of COVID-19 infection is continuously increasing with time, especially in the Americas, Europe, and Southeast Asia [1]. Although most people develop mild or uncomplicated forms of COVID-19, it has been estimated that approximately 14% of cases are associated with severe acute respiratory infection and may require hospitalization and oxygen support. Moreover, 5% of patients will require admission to an intensive care unit [2]. The COVID-19 pandemic has overwhelmed health systems worldwide. After discharge from hospital, some patients with COVID-19 continue to experience symptoms, which may last for months or even longer. These consequences include medical, physical, cognitive, and psychological problems. Although the long-term consequences are still unclear, recent studies have revealed that most patients (74%-87%) experience ongoing signs and symptoms 2-3 months after discharge from hospital, including fatigue, shortness of breath, impaired functions, and secondary mental problems [3,4]. Rehabilitation may contribute to patient recovery and is crucial in endowing patients with health improvements related to functional ability and quality of life.

For patients who have been unwell and sedentary for long periods, increased strength [5], aerobic ability [6], and exercise performance are vital to facilitate physiological [7], biochemical, psychological [8], and general recovery [9]. Considering the clinical conditions caused by prolonged immobilization and musculoskeletal deterioration, patients with COVID-19 need rehabilitation treatments following hospital discharge [10]. Exercise has direct effects on the cellular immune system; natural killer cells and T lymphocytes (T cells) become mobilized in the circulation through stress-induced shear stress and adrenergic signaling during exercise performance, providing protection and repair.

In addition to exercise intervention strategies, Chinese herbal medicines targeting gut microbiome dysbiosis have also been reported to improve immune function [11], facilitating patients’ recovery. The gut microbiome influences immune function and immune homeostasis both within the gut and systematically [12]. Chinese herbal medicines, the gut microbiome, and microbial metabolites regulate immune function and intestinal permeability involved in the pathological processes of virus-induced autoimmune diseases [11]. Restoring gut microbiome composition and its regulatory metabolites could be vital in boosting immune function and aiding recovery from COVID-19. Additionally, patients with COVID-19 experience loneliness, anxiety, depression, and decreased quality of life [13]. In summary, evidence suggests that exercise or Chinese medicines can help patients recover from virus-induced immune diseases and respiratory conditions such as pulmonary fibrosis. However, the potential beneficial individual and combined effects need further investigation.

In our proposed study, we will develop a new paradigm for the patient rehabilitation that is needed now and in the future. The specific aims of this project are (1) to investigate the effects of a 12-week programme involving cardiorespiratory exercise and Chinese herbal medicine, both singly and combined, on patients recovering from COVID-19 who exhibit pulmonary impairment and (2) to collect qualitative and quantitative data to examine the patients’ loneliness, anxiety, depression, quality of life, and mental health. A further aim will be to examine how Chinese herbal medicines as well as the gut microbiome and its metabolites regulate immune function, intestinal permeability, and possibly autoimmune deficiency in the pathological recovery and rehabilitation process. The specified study objectives and hypotheses are listed below:

Evaluate the effects of cardiorespiratory exercise and Chinese herbal medicine, both individually and in a combination, on rehabilitation on pulmonary function among patients with COVID-19 through four intervention groups, including a cardiorespiratory exercise plus Chinese herbal medicines group, a cardiorespiratory exercise group in isolation, a Chinese herbal medicines group, and a waiting list control group (primary outcome). We hypothesize that the combination of cardiorespiratory exercise and Chinese herbal medicines will more greatly facilitate the rehabilitation of patients with COVID-19.Reveal whether and how the gut microbiome plays a role in the effects of cardiorespiratory exercise and Chinese herbal medicines, both individually and in combination, on the rehabilitation of impaired pulmonary function. We hypothesize that the combination of cardiorespiratory exercise and Chinese herbal medicines will better modulate the gut microbiome and the related metabolites and thus better mediate the effects.Assess the effects of cardiorespiratory exercise and Chinese herbal medicines on immune functions, both individually and in combination, on the rehabilitation of other relevant symptoms and signs of COVID-19. We hypothesize that the combination of cardiorespiratory exercise and Chinese herbal medicines will better modulate the immune function and thus better mediate the effects.Evaluate the effects of cardiorespiratory exercise and Chinese herbal medicines, both individually and in combination, on recovery from mental health-related outcomes (loneliness, stress, anxiety, depression) and on quality of life (QoL). We hypothesize that the combination of cardiorespiratory exercise and Chinese herbal medicines will better help postdischarge patients in recovery from mental health-related outcomes and improve their QoL.Assess the lasting effects of cardiorespiratory exercise and Chinese herbal medicines after a 12-week follow-up period. We hypothesize that some effects (eg, dyspnea, mental health-related outcomes, QoL) will be sustainable, while others (outcomes sensitively responded to cardiorespiratory exercise, eg, physical fitness, lung function) will partially relapse after the intervention cessation.

## Methods

### Study Design

The proposed study will be a triple-blinded randomized controlled trial comprising four groups: (1) a cardiorespiratory exercise plus Chinese herbal medicines group, (2) a cardiorespiratory exercise group, (3) a Chinese herbal medicines group, and (4) a waiting list group. The target population will be postdischarge adult patients recovering from COVID-19 who were diagnosed with pulmonary impairments. Recruitment will take place in Hong Kong via our International Rehabilitation Network Center for Patients With COVID-19. The proposed rehabilitation period will last for 12 weeks, with a 12-week follow-up [14]. Primary outcomes will include the clinical symptoms of pulmonary fibrosis (dyspnea, fatigue, lung function, blood oxygen levels, immune function, blood coagulation, and related blood biochemistry). Blood biochemistry will be further analyzed using unique metabolomics techniques to identify potential synergies related to immune function response to the interventions [15]. We will investigate glucose metabolism and its association with the degree of infection and prognosis. We will also profile the gut microbial metabolome to establish associations between (virus-induced) dysbiosis and the outcomes of COVID-19 infection. Pulmonary function tests will be completed using clinical spirometry, as outlined by the American Thoracic Society. Blood gas levels, immune function, and coagulation levels of the patients will be measured pre- and post-intervention in venous blood samples [16]. The trial has been registered on ClinicalTrials.gov (NCT04572360). A flow diagram of the trial is shown in Figure 1.

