#### Cardiopulmonary Exercise

The CPET will be performed using the Vmax Encore V229. The CPET provides information concerning the level of exercise that the patient can perform without undue stress. The test results will guide the research team regarding the prescription of exercise for physical rehabilitation methodologies. It also provides quantitative evidence of the benefits of a rehabilitation program as well as information on the mechanisms involved. Improvement in exercise tolerance cannot be objectively assessed without CPET [36]. An incremental ergometry exercise test (Excalibur ergometer, Lode Ergometry), will be used to assess the responses of the cellular, cardiovascular, and ventilatory systems under precise conditions of metabolic stress. Breath by breath measurements of minute ventilation (VE), carbon dioxide output (VCO_2_), O_2_ uptake (VO_2_), VE/VCO_2_, VE/VO_2_, deviation in the responses from the pulmonary to cellular respiration and arterial blood gas, partial pressure of carbon dioxide (PCO_2_), and oxygen saturation as measured by pulse oximetry (SpO_2_, Sentec AG), will be monitored continuously during the exercise test. Depending on the physical condition of the patients, modification of the protocols to smaller work rate increments may be warranted. Intensities and durations will be specific to each individual to facilitate measurement and data capture. Before each test, the O_2_ and CO_2_ analyzers of the CPET system will be calibrated using standard gases (Gas 1: O_2_: 25.89%, CO_2_: 0%; Gas 2: O_2_: 16.44% CO_2_: 3.89%), and the flow volume integration system will be was calibrated by applying a standard volume (3 L) of gas at various flow rates. Canopy studies within the Vmax software suite will be used to validate the accuracy of the gas-exchange measurement instruments that measure VO_2_ and VCO_2_ using the methanol burning technique. The ratio of VCO_2_ to VO_2_ in the combustion of methanol yields a respiratory quotient (RQ) of 0.667. We will use a 3% difference as the accuracy threshold for measured RQ (RQ range of 0.647-0.687).

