#### Blood Biochemistry

Venous blood will be drawn at 3 time points, namely at pretreatment, at posttreatment, and after the 12-week follow-up. After coagulation at room temperature for 30 minutes, the samples will be centrifuged at 3000 rpm for 20 minutes. Serum as the supernatant will be extracted and stored at –80 ˚C until assay. Serum levels of insulin will be assessed by a commercially available enzyme-linked immunosorbent assay (ELISA) kit (Merck & Co). Serum will be isolated by centrifugation (1000 rpm for 30 minutes, 4 °C) and stored at –80 °C until analysis. The prothrombin time test will be used to measure blood coagulation. Venous blood will be collected by venepuncture in a tube with sodium citrate. Plasma will be isolated after centrifugation at 1000 rpm for 30 minutes at 4 °C. Thromboplastin will be added to the plasma and maintained at 37 °C for 2 minutes. Calcium chloride will be added to the mixture, and the plasma will be allowed to coagulate. The time needed for the coagulation will be recorded as the prothrombin time.

Flow cytometry for counts of main lymphocyte subpopulations (CD3, CD4, CD8, CD19, and CD16+CD56 T cells) will be performed to test immune function. Venous blood will be stored in tubes with EDTA (anticoagulant). 100 µL of blood will be stained within 24 hours of sampling by the BD Multitest 6-color TBNK reagent (BD Biosciences). The lymphocytes with the antigens CD3, CD4, CD8, CD19, and CD16+CD56, which are the main populations of lymphocytes, will be labelled by a fluorochrome-conjugated antibody in the reagent. The whole blood will be incubated in the reagent at room temperature for 30 minutes, and red blood cells will be lysed with ammonium chloride solution. Cell sorting and analysis will be performed with a BD Accuri C6 flow cytometer (BD Biosciences). Each subpopulation of lymphocytes will be expressed in absolute value and percentage of total lymphocytes.

As suggested by Hacimusalar and Eşel [38], the following markers related to emotional disturbances will be studied.

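### The primary blood-oxygen outcome has no single defined measurement, and venous blood, the only specimen stated for blood gases, would not show how well the lungs oxygenate blood

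*Protocol article*

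**What the plan says.** **Status of the outcome.** The abstract's Methods paragraph states: "Primary outcomes include dyspnea, fatigue, lung function, pulmonary function, blood oxygen levels, immune function, blood coagulation, and related blood biochemistry". Study Design gives nearly the same list, presented as clinical symptoms of pulmonary fibrosis: "dyspnea, fatigue, lung function, blood oxygen levels, immune function, blood coagulation, and related blood biochemistry".

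**How it might be measured.** Three places bear on this.

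- Study Design: "Blood gas levels, immune function, and coagulation levels of the patients will be measured pre- and post-intervention in venous blood samples".
- Cardiopulmonary Exercise: the signals followed during the cardiopulmonary exercise test (CPET) include a phrase that runs from "pulmonary to cellular respiration and arterial blood gas, partial pressure of carbon dioxide" on to "oxygen saturation as measured by pulse oximetry (SpO_2_, Sentec AG), will be monitored continuously during the exercise test".
- Outcomes, Table 2: one row combines the CPET with blood gas and lists PCO2 and PO2. It gives no specimen, and SpO2 does not appear in the table.

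**When.** Study Design speaks of before and after the intervention. The Outcomes section puts every measurement at baseline, week 13 and week 25. Blood Biochemistry agrees: "Venous blood will be drawn at 3 time points, namely at pretreatment, at posttreatment, and after the 12-week follow-up".

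**The concern.** Because Study Design presents blood oxygen as a feature of pulmonary fibrosis, the quantity of interest is how well the lungs oxygenate blood. The one sentence that assigns a blood specimen to blood gases assigns venous blood. Peripheral venous blood has already passed through tissue, so its PO2 depends on how much oxygen the tissue removed and on local blood flow, as well as on what the lungs supplied.

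This matters particularly for a trial of exercise. The Discussion itself says that long-term interval training can improve peripheral muscle capacity. If training changes extraction, venous PO2 could differ between exercise and non-exercise arms with no difference in the lungs, and possibly in the direction opposite to benefit. Such a difference could not be read as an effect on oxygenation.

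There is a second risk. While venous gas, arterial gas and SpO2 during exercise all remain candidates for one primary outcome, the choice can still be made after results are seen.

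**Working it through.** No arithmetic decides this point, so the passages are compared directly.

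| Source in the protocol article | Variable | Specimen or method | Condition | Timing |
|---|---|---|---|---|
| Abstract; Study Design outcome list | Blood oxygen | Not stated | Not stated | Abstract: before treatment, weeks 13 and 25 |
| Study Design, sampling sentence | Blood gas | Venous blood | Not stated | Before and after the intervention |
| Cardiopulmonary Exercise | Arterial gas, PCO2, SpO2 | Pulse oximetry for SpO2; no arterial sampling described | During the CPET | Continuous within the test |
| Outcomes, Table 2 | PCO2, PO2 | Not stated | Row shared with the CPET | Baseline, weeks 13 and 25 |

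1. **Is one variable identifiable?** No. Specimen, method and condition differ between rows, and nothing links the primary outcome to one of them.
2. **Does the venous sentence concern this outcome?** Probably, but this is an inference. It says blood gas, not blood oxygen. It stands in the same paragraph as the primary outcome list, and Table 2 puts PO2 under blood gas.
3. **Would venous PO2 serve?** No. It is taken after tissue extraction, so it does not isolate what the lungs do. This is general physiology and needs no figure from outside.
4. **Is there already a candidate that avoids venous blood?** Yes. SpO2 is recorded during the CPET, but it is missing from Table 2 and not designated as the outcome. No resting value is stated.
5. **Could the lowest SpO2 in the CPET be used?** Not safely. The test is incremental, and its increments, intensities and durations may be adapted to the patient. The lowest value therefore depends on the workload reached, which training can raise. A patient who improves may go further and desaturate more.
6. **How much of the trial is affected?** One of eight domains by the abstract's count, or one of seven by Study Design's, for all 172 patients.
7. **Is the sample size affected?** No. For an effect size of 0.8, two-sided 0.05 and 90% power, a two-sample t-test needs 33.83, so 34 per group. Then 34 / 0.8 = 42.5, so 43 per group, and 4 × 43 = 172, as stated. That calculation rests on dyspnea and exercise capacity.

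**The case against.** The strongest reply is that these are loosely worded descriptions of different things. The exercise section describes no arterial puncture. Its reference to arterial gas sits in an unclear phrase within a list of continuously monitored signals, and may mean physiological responses during exercise, separate from any venous sample. Two measurements under different conditions do not contradict each other. The primary outcome might also simply be SpO2, in which case the argument about venous PO2 falls away. This part stands: a reader might infer that the plan definitely makes venous PO2 a primary outcome, or that it flatly contradicts itself on the specimen, and the text supports neither. It does leave the primary variable unidentified, with venous blood the only specimen stated for blood gases.

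A reader might also infer from the Study Design timing that there will be no week-25 blood gas value, so that the lasting-effects objective cannot be met for this outcome. The documents do not support that. The abstract and Outcomes section give three visits, Blood Biochemistry gives three venous draws, and the schedule table marks both the CPET and the blood tests at follow-up. The same Study Design sentence covers immune function and coagulation, whose venous blood is clearly drawn three times. Its timing is best read as loose summary wording.

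It is also fair to say that a condensed article may leave assay detail to the full protocol, and that Table 2 is described as not exhaustive. The absence of a blood gas step from Blood Biochemistry therefore carries no weight here. The point rests on what the article does state: a specimen unsuited to the outcome's apparent purpose.

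Finally, this outcome does not drive the trial. The first objective attaches the primary label to pulmonary function. That limits the seriousness but does not remove the defect, because the abstract and Study Design both list blood oxygen as primary.

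**Conclusion.** The point holds in a limited form. A listed primary outcome has no single defined measurement, and the only specimen stated for blood gases would not measure lung oxygenation if it were used.

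The conclusion rests on two assumptions: that blood gas in the sampling sentence is meant to supply the blood-oxygen outcome, which the placing of the sentence and Table 2 suggest but do not prove; and that the outcome is meant to reflect lung function, which follows from its presentation as a feature of pulmonary fibrosis. If the first is wrong, the outcome is still undefined.

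The documents give no venous-arterial difference and no expected training effect on extraction, so neither the size nor the direction of a bias can be computed. The change should be made, but the point does not threaten the sample size or the other primary domains.

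**What to change.** Reconcile Study Design, Table 2 and Cardiopulmonary Exercise as follows.

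- **Name one oxygenation variable that does not use venous blood**, with its method and condition. Two workable examples, both using the existing oximetry device, are SpO2 at rest just before the CPET, or SpO2 at a fixed submaximal work rate common to a patient's three tests. Choose one. Do not use the lowest SpO2, for the reason given in the working.
- **Do not use venous PO2 as the oxygenation outcome.** Take blood gas out of the venous sentence, or say what other purpose it serves. State the specimen for PO2 if it stays in Table 2.
- **Add SpO2 to Table 2.**
- **Replace the before-and-after timing in Study Design** with baseline, week 13 and week 25. This aligns the wording with the Outcomes section and does not add a visit.

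The article says that recruitment is under way, so the choice should be fixed and dated before anyone sees outcome data by group.

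The cost is mostly rewording. One resting or matched-workload reading must be recorded at each visit, and the trial gives up a partial pressure as its primary oxygenation variable. A resting reading is not shown as already recorded, so it may be missing for patients tested before the change. A matched-workload value might be recovered from the continuous exercise recordings, if those were stored.
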